### Subject identification and recruitment

Any patient with a blunt injury undergoing emergency A/P CT imaging will be identified as a study subject. Cases will be formally identified when the treating physician requests A/P CT imaging. At this point, the ordering clinician will be approached by a study research assistant and asked to complete a survey that documents the presence or absence of individual risk criterion. The research assistant will also record the patient demographic and identifying information needed to complete the enrollment.

### Human subjects considerations and procedures

The study will collect data from the routine examination and evaluation of patients with blunt trauma. Every patient presenting with blunt trauma will initially undergo a clinical evaluation. The examining physicians will determine whether imaging is indicated based upon existing institutional treatment protocols and/or individual physician clinical judgment. There will be no study criteria to perform or abstain from imaging any patient, and such decisions will be left entirely to the discretion of the treating physicians. Because the study collects information from routine examinations, does not alter the care of individual patients, and will not retain or release identifying information on any individual, it meets the criteria for exemption from informed consent. The study has completed human subjects institutional review and been granted exemption of informed consent through the UCLA IRB and at the participating centers.

### Data collection

Our collected data will include patient demographic information (date, time, age, sex, and race) and the presence or absence of each individual study variable. Each record will also carry embedded information indicating the identity of the institution producing the data. Because we want to increase the external validity of the study to reflect general practice, we will not provide rigid definitions for any of the individual data elements. This will help ensure that the validated low-risk criteria are widely applicable; clinicians will be asked to judge whether these elements are present on the basis of their routine clinical assessment, as they would when eventually applying the decision instruments. However, for purposes of clarification, we will provide clinicians with general descriptions of each clinical characteristic. These will be presented as informational material to all sites and will be reviewed with clinicians during in-service training sessions conducted before the beginning of the study. Potential predictor variables have been selected according to *a priori* determined associations with SAPI and acceptable inter-rater reliability [8, 17, 21, 42–45]. Additional demographic, historical, vital sign, imaging, and outcome data will also be collected (S1 File presents our data collection instrument for candidate criteria).

Our study will also collect A/P CT imaging and outcome results for each patient. All patients will have received A/P CT imaging, and may have received plain pelvic imaging. These initial studies may be supplemented by any other imaging studies deemed necessary by clinicians involved in the patient’s care.

Clinical radiologist at each site will review the x-ray and CT images and prepare final radiographic reports. We will review the final radiographic interpretations to determine whether an individual has sustained a SAPI, but will classify injuries as major, minor, or insignificant based on review of procedural records.

### Phase 1: Derivation of optimal low-risk decision instrument(s) for A/P CT imaging

The first step in identifying suitable risk criteria is to assess the reproducibility of the assessments on the presence or absence of each individual criterion. This is achieved by having paired physicians performed independent evaluations of each criterion on patients undergoing A/P CT imaging, and comparing the results of the two assessments for each individual criterion.

For our study, each of two paired physicians will independently determine whether an individual patient exhibits any of the following potential predictor characteristics: 1) abdominal pain or tenderness, 2) flank pain or tenderness, 3) pelvic pain or tenderness, 4) hip or iliac pain or tenderness, 5) midline lumbar spine or sacral pain, 6) abdominal distention, 7) abdominal or pelvic bruising, 8) abdominal or pelvic abrasion, 9) evidence of genitourinary trauma, 10) abnormal alertness, 11) evidence of intoxication, 12) distracting painful injury, 13) hypotension, 14) tachycardia, 15) unstable vital signs, 16) low hemoglobin or hematocrit, 17) falling hemoglobin or hematocrit, 18) dangerous mechanism of injury, 19) abnormal plain radiography. For analytic purposes, each variable will be considered negative (normal) unless it can be assessed and found to be abnormal. Thus, variables that cannot be measured in an individual patient (such as pain in an unconscious individual) will be documented as “unable to assess” and treated statistically as negative. This type of imputation has the effect of ensuring that the final derivation process is based on actual observed criteria, and while this may decrease the observed sensitivity of the derivation rule (some patients may have exhibited criteria that were not assessed and been classified as not low-risk if the criteria had been assessed), it leads to a more robust derivation.

We will employ Scott’s pi statistic to assess physician inter-rater reliability of the independent assessments of each criterion and designate those exhibiting a point measure of 0.40, or greater, as exhibiting substantial inter-rater agreement and suitable for inclusion in the decision instrument. S1 File contains a copy of the survey instrument we will use to record criterion assessments.

We will assign a final clinical outcome for each patient based on the results of A/P CT imaging as well as the patient’s hospital course. Patients who we designate as having injuries must have injuries evident on CT imaging. This reflects the fact that if injuries are not apparent on CT imaging, it is immaterial whether the patient underwent such imaging. Furthermore, we will classify each patient as having, in order of increasing severity: 1—no injuries (no injuries evident on CT); 2—insignificant injuries (e.g., minor bruising, small hematomas, or isolated small avulsion fractures); 3—clinically minor injuries (significant injuries that require no specific intervention); and 4—clinically major injuries (significant injuries that require specific intervention or result in patient death). Our final outcome classification will be based on the most severe type of injury sustained by each patient. We will concatenate our final outcome assignments with the criterion assessments to create our final analysis database.

We will apply chi-squared binary recursive partitioning to this data set to identify separate combinations of criteria that identify both major and minor significant abdominopelvic injuries with > 98% sensitivity and > 98% NPV, assuming such combinations exist. If more than one combination of variables exhibits the requisite sensitivity and negative predictive values for injury, the combination with the highest specificity will be adopted as the optimal low-risk decision instruments.

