## Objectives

### General design

In this prospective, cohort, multi-center study we seek to develop an imaging decision tool that will enable clinicians to identify patients with blunt trauma who are at “very low-risk” for clinically significant A/P injuries. Implementation of the decision tool will require clinicians to assess the presence or absence of specific clinical findings. Patients with a full assessment of all criteria and who exhibit none of the clinical findings will be designated as “very low-risk”. Patients who exhibit one or more of the clinical findings, as well as those for whom a complete assessment of criteria cannot be completed, will be designated as “not low-risk.” Patients who are designated as very low-risk will have negligible potential to harbor significant A/P injuries, will receive no benefit from A/P CT imaging, and will therefore be safe to exclude from A/P CT imaging. All other patients remain candidates for imaging. It is worth noting that while our project focuses on developing a rule for combined A/P CT imaging, the rule will also be suitable for evaluating patients for isolated abdominal or isolated pelvic imaging. This is a reflection of the fact that patients who are designated as low risk by our instrument will have negligible risk of either abdominal or pelvic injury, and can safely be excluded from abdominal-pelvic imaging, isolated abdominal imaging, or isolated pelvic imaging.

Classification by an optimal decision instrument will reflect a balance between the risk of imaging (malignant transformation from exposure to ionizing radiation), the costs of CT, and the risks of not imaging (potential harm from unrecognized significant injuries). Because the rate of lethal malignant transformation is low, the decision tool must exhibit high sensitivity to ensure that the missed injury rate is very low, and that virtually all patients with significant injuries are designated as “not low risk.”

To be clinically useful, the decision tool must also assign low-risk classification to as many uninjured patients as possible. This is equivalent to requiring the tool to produce as few false positive results as possible, or equivalently, exhibit high specificity. The proportion of patients who can safely be spared imaging is directly related to the instrument’s specificity, so the development process will focus on identifying a tool with the highest possible specificity.

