### Inclusion/Exclusion criteria

The study will be observational by design and will not alter the care or management of blunt trauma patients. Medical management will be determined by treating physicians using current standards of care.

To reduce the potential for bias, the study will seek to enroll all victims of blunt injury who undergo A/P CT imaging as part of their ED trauma evaluation. This may include adult patients of all ages, including the elderly, any and all races, both sexes, women who are pregnant or have childbearing capacity, and any other representative demographic or social groups that may present among patients with blunt injuries. An individual will become eligible for the study when the treating physician determines that A/P CT imaging is needed as part of their trauma evaluation. This eligibility criterion aligns with our goal to develop instruments that will be used to safely decrease CT imaging–the fact that clinicians have already decided to order imaging in enrolled patients *en face* supports the notion that our instruments may only serve to decrease CT ordering.

There will be no exclusion criteria. However, while the study will seek to enroll all patients with blunt injury who undergo A/P CT imaging, treating physicians will be able to waive data collection and immediately obtain imaging on any patient they feel is unstable or in whom they cannot complete their study evaluation prior to imaging. These patients will be designated as “unstable,” with stability being an implicit criterion of the rule. Physicians will be requested to complete data entry for these patients at their earliest opportunity, ideally before imaging results are known. This process will not threaten the study validity, however, because instability will be an *a priori* criterion, while blood pressure and heart rate parameters consistent with instability are, themselves, candidate criteria and may become part of the final decision instrument.

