### Phase 2: Validation of low-risk decision instruments for A/P CT imaging

At the completion of the derivation phase, we will begin enrolling patients into a validation study to assess, and attempt to validate, the test characteristics of our newly developed decision instruments. We will record the presence or absence of the individual criteria of the new decision tool(s), and we will combine these assessments with results of A/P CT imaging and clinical course to form our validation data set. We will evaluate criteria in the validation phase using methodology similar to that used in the derivation phase, although two aspects of assessment will change between the two phases. The first change reflects the reduced number of number of criteria assessments that need to be completed on each patient in the validation phase, as clinicians will only need to assess criteria included in the derived rule(s). A second important difference between the two phases involves the handling of un-assessed criteria. In the validation phase, and in the ultimate application of the rule, each criterion will be considered positive (abnormal) unless it can be assessed and found to be normal. Thus, variables that cannot be measured in an individual patient (such as pain in an unconscious individual) will be documented as “unable to assess” and treated analytically as positive. This assures that low-risk status, and exclusion from imaging, is based on actual observations of normal findings, and prevents low-risk assignment on the basis of inadequate or incomplete assessment.

Clinical outcomes and injury assessments in the validation phase will be identical to those completed in the derivation phase.

We will assign risk status to each patient based on the criteria assessments, and use these risk assessments in combination with outcome assignments to calculate point measures and 95% confidence intervals for sensitivity, negative predictive value, specificity, and estimated potential reductions in imaging that might be achieved by implementation of each of the rules (both minor and major injuries).

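### Derivation scores un-assessed criteria as negative, so its success test and specificity ranking judge a different classifier from the rule that is validated and used

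*Protocol article*

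**What the plan says.** Three sections of the protocol article govern criteria that could not be assessed.

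- **General design** defines the rule. Patients with any finding, and "those for whom a complete assessment of criteria cannot be completed, will be designated as" not low-risk.
- **Phase 1 (derivation)** codes the other way: "For analytic purposes, each variable will be considered negative (normal) unless it can be assessed and found to be abnormal". The stated reason is that derivation should rest on findings actually observed. One consequence is admitted: "while this may decrease the observed sensitivity of the derivation rule". Specificity is not mentioned.
- **Phase 2 (validation)** returns to the definition: "each criterion will be considered positive (abnormal) unless it can be assessed and found to be normal". This is said to hold in eventual use as well, and it is presented openly as a change between phases.

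Two decisions are taken on the derivation data. Phase 1 adopts, among combinations that meet the thresholds, the one with the highest specificity. The section on formulating the decision instruments stops successfully when every injured patient is captured (Case 1), or otherwise when the lower confidence limit for sensitivity is above 98% (Cases 2 and 3). Neither section re-scores the data under the Phase 2 convention first.

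Inclusion/Exclusion criteria adds that "treating physicians will be able to waive data collection and immediately obtain imaging on any patient they feel is unstable". Such patients are labelled unstable, and instability is named as a criterion fixed in advance. It also says: "Physicians will be requested to complete data entry for these patients at their earliest opportunity, ideally before imaging results are known".

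**The concern.** Coding un-assessed as negative is a defensible way to choose splits, because a criterion then earns its place only through findings that were seen. Judging and ranking the finished rules is a different step. There, the quantity of interest is how the rule will classify patients, and the rule sends incompletely assessed patients to the not-low-risk group. Under derivation coding, the same patients count as low-risk if nothing abnormal was recorded.

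Two decisions are at stake. A rule that would miss nobody in use can be declared unsuccessful, or be loaded with extra criteria, because of misses that exist only in the coding. And a combination built on findings that often cannot be assessed, such as pain or tenderness, can win the specificity ranking on the strength of patients it would not spare. Validation would then report the chosen rule correctly, but could not recover the rival that was passed over.

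Waived patients add to this. The article does not say how the instability designation enters the derivation scoring, and late entry is only ideally made before the CT result is known.

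**Working it through.** **1. Direction.** Fix a set of criteria and a data set. Changing an un-assessed value from negative to positive can only move a patient from low-risk to not low-risk. An injured patient who moves goes from false negative to true positive; an uninjured one goes from true negative to false positive. So, compared with the rule as used, negative coding gives sensitivity that is equal or lower and specificity that is equal or higher.

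**2. The plan's own figure.** The sample size section uses the exact lower limit with no misses, which reduces to (α/2)^(1/N). With α = 0.05 and a limit of 0.98, N ≥ ln(0.025)/ln(0.98) = 182.6, so 183. The stated 317 does not reproduce. It corresponds to a tail of 0.98^317 = 0.00165, which the article does not state. That is a separate matter; 317 is used below as the planned number of injured patients per phase.

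**3. Success test.** Exact 95% lower limits (tail 0.025) for 317 injured patients:

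| Misses | Lower limit | Above 98%? |
|---|---|---|
| 0 | 0.025^(1/317) = 98.84% | yes |
| 1 | 98.26% | yes |
| 2 | 97.74% | no |

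Two misses created by coding (2/317 = 0.63%) therefore fail the test. At the stricter tail implied by 317, one miss already fails (97.30%).

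Now take a rule that truly misses nobody, and let r be the share of injured patients who are coded negative throughout because something was not assessed. The chance of passing is the chance of at most one such patient: (1−r)^317 + 317·r·(1−r)^316. The values of r are assumptions.

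| r | Chance of passing |
|---|---|
| 0.1% | 96% |
| 0.25% | 81% |
| 0.5% | 53% |
| 1% | 17% |
| 2% | 1.2% |

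**4. Case 1.** This ending requires every injured patient to be captured. One injured patient coded negative on all candidate criteria can never be captured, so Case 1 becomes unreachable and the partitioning runs on.

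**5. Specificity.** The sample size section plans 6,340 patients per phase, 317 of them injured, and takes about 10% as free of all criteria. That gives 6,340 − 317 = 6,023 uninjured and 634 low-risk. Assume that all 634 are uninjured and that the 10% reflects negative coding; the article does not say so. Apparent specificity is 634/6,023 = 10.5%. If a share u of the uninjured is low-risk only because of the coding, specificity in use is (634 − 6,023u)/6,023. The values of u are assumptions.

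| u | Specificity in use | Fewer spared than derivation shows |
|---|---|---|
| 1% | 9.5% | 9.5% |
| 2% | 8.5% | 19% |
| 3% | 7.5% | 28.5% |
| 5% | 5.5% | 47.5% |

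**6. Ranking.** An assumed example: combination A shows 12%, of which 4 points come from un-assessed patients, so 8% in use. Combination B shows 10%, of which 1 point does, so 9% in use. Derivation adopts A, although B spares more.

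**The case against.** The difference is deliberate, disclosed and explained, and its effect on sensitivity is conceded. Its direction is conservative: negative coding cannot pass an insensitive rule. Performance is judged in Phase 2 with the rule's own scoring, and Core methods says the potential to reduce imaging will be read from validation specificity. The rates used above are assumed, and two misses from any cause would fail the test. Positive scoring also has a cost, since it credits a criterion with catching an injury simply because it was missing.

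Most of this stands as a limit on the point. It does not remove it. The reason given supports the coding for growing the partition, not for the success test or the ranking, and the upward pull on specificity is nowhere acknowledged although specificity decides which rule is adopted.

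A reader might go further and infer that unstable patients whose data collection was waived automatically become false misses. The document does not support that. It names instability as a criterion fixed in advance and asks for the data to be entered later. Tachycardia and unstable vital signs did fall below the 0.40 agreement threshold, but hypotension (0.63), abnormal alertness (0.48), intoxication (0.68) and distracting injury (0.43) passed. The article's own example, the unconscious patient, would normally be positive on alertness if that criterion is in the rule. A waived patient becomes a false miss only if injured, with no abnormal criterion recorded, and with the instability criterion left out of the derivation scoring. The article does not settle the last condition: the Phase 1 coding makes no exception, and the instability designation is not among the 19 listed variables.

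**Conclusion.** The point holds in limited form. The success test and the specificity choice in derivation are applied to a classifier that differs from the rule as defined, validated and used. The possible consequences are a false failure of derivation, an unreachable Case 1, and adoption of a combination whose specificity in use is below a rival's.

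The firm number is the tolerance: at 317 injured patients and a 0.025 tail, one coding-made miss passes and two fail. How often that would happen, and how far specificity is inflated, cannot be determined, because the article gives no rate of un-assessed criteria; the tables show only what assumed rates would do.

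It would be wrong to conclude that the final performance figures are biased or that an unsafe rule could be let through by this coding. The sensitivity error runs in the cautious direction, and the validation estimates use the correct scoring.

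**What to change.** - Keep negative coding for growing the partition.
- Before the success test and the specificity choice, re-score every candidate rule with un-assessed counted as positive, as in Phase 2. Report derivation sensitivity, NPV and specificity on that basis, with the negative-coded figures alongside.
- State that the instability designation scores as positive in both phases.
- Flag criteria entered after the CT result is known, and run a sensitivity analysis without those patients. Do not recode late entries as un-assessed: counted as positive, they would make injured waived patients automatic true positives.

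The cost is analysis wording and, if the data form lacks one, a mark for entry before or after the CT result. No extra patients are needed. There are two downsides. Derivation specificity will look lower, and the sensitivity gate becomes less conservative than under negative coding, which is why both sets of figures should be shown.

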### Phase 2: Validation of low-risk decision instruments for A/P CT imaging

At the completion of the derivation phase, we will begin enrolling patients into a validation study to assess, and attempt to validate, the test characteristics of our newly developed decision instruments. We will record the presence or absence of the individual criteria of the new decision tool(s), and we will combine these assessments with results of A/P CT imaging and clinical course to form our validation data set. We will evaluate criteria in the validation phase using methodology similar to that used in the derivation phase, although two aspects of assessment will change between the two phases. The first change reflects the reduced number of number of criteria assessments that need to be completed on each patient in the validation phase, as clinicians will only need to assess criteria included in the derived rule(s). A second important difference between the two phases involves the handling of un-assessed criteria. In the validation phase, and in the ultimate application of the rule, each criterion will be considered positive (abnormal) unless it can be assessed and found to be normal. Thus, variables that cannot be measured in an individual patient (such as pain in an unconscious individual) will be documented as “unable to assess” and treated analytically as positive. This assures that low-risk status, and exclusion from imaging, is based on actual observations of normal findings, and prevents low-risk assignment on the basis of inadequate or incomplete assessment.

Clinical outcomes and injury assessments in the validation phase will be identical to those completed in the derivation phase.

We will assign risk status to each patient based on the criteria assessments, and use these risk assessments in combination with outcome assignments to calculate point measures and 95% confidence intervals for sensitivity, negative predictive value, specificity, and estimated potential reductions in imaging that might be achieved by implementation of each of the rules (both minor and major injuries).

